Carbon monoxide (CO) monitor will be used to assess the exhaled CO level of the study participants during each visit. The cutoff point will be six parts per million or less for nonsmokers and more than six parts per million for smokers [15]. Cotinine is a metabolite of nicotine with a long half-life (15–19 hours) that can be measured in body fluids such as saliva, urine and plasma. Measurement of salivary cotinine as an indicator of tobacco use, exposure to secondhand smoke or use of pharmaceutical nicotine is commonly used in population studies, given the ease of sample collection and minimal discomfort to study subjects.[13]. Hence, saliva cotinine test will be done to assess the smoking status of the participants during baseline and end-line of the study. Saliva cotinine test results will be considered as the biochemical verification for smoking status. However, carbon monoxide levels will be a complementary test to support the evidence for smoking status of the participants. This is because the concentration of cotinine measured in plasma, saliva, or urine has the highest sensitivity and specificity to detect smokers in comparison to CO concentration in blood and expired air due to relatively lower sensitivity than cotinine [14]

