**E. Primary Outcomes:**

The primary clinical outcome will be the binary smoking cessation; abstinence or non-abstinence assessed at 12 months from the starting point of intervention. Non-abstinence will be defined as self-reported smoking anytime during the intervention or follow up and a positive salivary cotinine test.

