**I. Study tools:**

A semi-structured questionnaire will be developed to capture information about the participants' socio-demographic factors, smoking history, current smoking status, tobacco dependence score, medical history, follow-up of treatment, and stage of transtheoretical model during each visit. The participants will be assessed for carbon monoxide levels, body weight in kg during each visit and salivary cotinine test during the start and end of the follow-up. A pilot study will be conducted on ten participants to test the validity and feasibility of the tools. Processes of change questionnaire, fagerstorm test questionnaire, medication adherence rating scale, and clinician rating scale will be used in the study. Predictors of smoking cessation such as concern about own health, others' health due to passive smoking, smoking expenses, past quit attempts, etc will be measured. [16].

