| Health related quality of life                                           | 0-Day, 6 months, 12 months                                                                                                                                                                                                                                                                                                                   | 0-Day, 6 months, 12 months                                                                                                                                                                                                                                                                               |
| Saliva cotinine test                                                     | 0-day, Month- 3, 6, 12                                                                                                                                                                                                                                                                                                                       | 0-day, Month- 3, 6, 12                                                                                                                                                                                                                                                                                   |

**K.Statistical Analysis:** The collected information will be summarized by using frequency and percentage for qualitative data, mean and standard Deviation for quantitative data. To compare the outcome measures, quantitative before and after intervention, paired-t test will be used. If data is not following normal distribution, Wilcoxon Signed Rank test will be used. To compare qualitative outcomes, Chi-square test or Fischer exact test will be used. To compare the difference in outcome measures between two intervention groups, independent sample 't' test will be used. If data is not following normal distribution, Mann Whitney test will be used. The P value less than 0.05 will be considered as statistically significant.

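### Smoking over 12 months is the primary endpoint, but the cotinine schedule contradicts itself and exhaled CO has no place in the definition, so smoking that is denied but shows on CO at month 9 can count as abstinence

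*Protocol*

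**What the plan says.** Section E (Primary Outcomes) sets a binary outcome, "abstinence or non-abstinence assessed at 12 months from the starting point of intervention", and adds: "Non-abstinence will be defined as self-reported smoking anytime during the intervention or follow up and a positive salivary cotinine test".

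The protocol gives two cotinine schedules:
- **Start and end only.** Section D: "saliva cotinine test will be done to assess the smoking status of the participants during baseline and end-line of the study". Section I (Study tools): "salivary cotinine test during the start and end of the follow-up".
- **Four tests.** Section J (Therapy protocol): "0-day, Month- 3, 6, 12". Item 4 of the budget justification pays for four kits per participant at the same times.

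Section D gives cotinine a half-life of 15 to 19 hours, names it as the verifying test, and notes that it also reflects secondhand smoke and medicinal nicotine. CO is taken at every visit, which section J lists as day 0 and months 1, 3, 6, 9 and 12. Up to 6 ppm is a nonsmoker and more than 6 ppm a smoker. Its role is limited: "carbon monoxide levels will be a complementary test". Section E does not mention CO.

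**The concern.** The outcome covers "self-reported smoking anytime during the intervention or follow up", which is about a year. The test that verifies it reaches back only a few days, and the protocol does not settle how often it is done. CO, which the trial collects at more visits and for which it has its own cutoff, has no stated effect on the outcome. A participant can therefore hold an objective positive reading on file and still be classed as abstinent on their own word.

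Two things are at stake. Missed smoking raises the abstinence rate in whichever arm it occurs, and the comparison can shift if denial differs between arms. Also, under the start-and-end schedule the 3- and 6-month cessation outcomes in section F have no cotinine check at all.

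**Working it through.** **1. How far back one cotinine test reaches.** Window = half-life × log2(starting level / cutoff). The half-life of 15 to 19 h is from section D. The protocol gives no cotinine level or cutoff, so I assume 100 to 400 ng/mL in a smoker and a cutoff of 10 to 30 ng/mL.
- Shortest: 15 h × log2(100/30) = 15 × 1.74 = 26 h, or 1.1 days.
- Longest: 19 h × log2(400/10) = 19 × 5.32 = 101 h, or 4.2 days.
- Share of a year: 1.1/365 = 0.3% to 4.2/365 = 1.2% for one test, and at most 3 × 4.2/365 = 3.5% for three post-baseline tests.

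**2. What the section E rule does at month 12.**

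| Self-report | Cotinine | Literal 'and' | Either finding suffices |
|---|---|---|---|
| Admits | Positive | Non-abstinent | Non-abstinent |
| Admits | Negative | Abstinent | Non-abstinent |
| Denies | Positive | Abstinent | Non-abstinent |
| Denies | Negative | Abstinent | Abstinent |

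Under the literal wording, denial alone gives abstinence whatever cotinine shows.

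**3. Two cases, both denying smoking and cotinine-negative at month 12.**

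| Case | Start and end, 'and' | Start and end, either | Four tests, 'and' | Four tests, either |
|---|---|---|---|---|
| A: smoking resumes after month 6; CO above 6 ppm at month 9 | Abstinent | Abstinent | Abstinent | Abstinent |
| B: smoking at months 6 and 9 | Abstinent | Abstinent | Abstinent | Non-abstinent, if month 6 cotinine counts |

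Case A assumes that the month 3 and month 6 cotinine tests do not themselves count against the participant. It passes in all four combinations because neither schedule has cotinine at month 9 and section E does not use CO.

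**4. Why earlier cotinine needs a condition.** The experimental arm is scheduled nicotine for 4 + 12 = 16 weeks, or 112 days (112/30.44 = 3.7 months). If months are counted from the start of treatment, a month 3 cotinine falls within treatment and cannot separate smoking from study nicotine. Section D also lets participants who are not ready to quit be counselled with no stated time limit, so some may still be using nicotine at month 6.

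**5. What missed smoking could do (illustration only).** Section G plans on 47.5% v 27.5%, two-sided 5%, 80% power. With pooled variance, n = [1.96√(2 × 0.375 × 0.625) + 0.842√(0.475 × 0.525 + 0.275 × 0.725)]² / 0.20² = 90.8, so 91 per arm. That reproduces the protocol's figure.

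Let a share m of true non-abstainers be counted as abstinent, so that p becomes p + m(1 − p). The protocol gives no value for m.
- Equal m = 10%: 52.75% v 34.75%. The difference falls from 20 to 18 points, and power at 91 per arm from 80.1% to 69.0%.
- Equal m = 20%: 58.0% v 42.0%, difference 16 points, power 58.0%.
- m = 10% experimental, 20% control: 52.75% − 42.0% = 10.75 points.
- m = 20% experimental, 10% control: 58.0% − 34.75% = 23.25 points.

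Equal misclassification shrinks the difference. Unequal misclassification can move it either way.

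**The case against.** The strongest reply is that no marker in the protocol covers a year. CO is also a point measure, so adding it still leaves most of follow-up resting on self-report. That is right: the change catches smoking around visits and not between them.

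Section D also gives a reason for preferring cotinine, namely better sensitivity and specificity. That supports cotinine as the main test at month 12. It does not explain why a CO reading above the protocol's own cutoff at month 9, where there is no cotinine, should have no effect. To call CO ignored would be too strong, since it is a supporting test. What is missing is a rule for when it disagrees with self-report. A statistical analysis plan might hold such a rule, but section E already fixes the definition without CO, and the cotinine schedule decides which samples are collected.

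A reader might infer that every denied mid-trial relapse passes as abstinence. The documents do not support that: case B is caught under the four-test schedule if either finding suffices. A reader might also infer that abstinence is inflated by a known amount or in favour of one arm. Any such figure only restates an assumed denial rate. Only the experimental arm wears patches before the quit date, and no placebo is described, so different reporting by arm is plausible despite the blinding stated in section H. It is not shown.

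Finally, letting any positive month 6 cotinine override self-report could class abstinent people still on nicotine as smokers. That stands, and it limits the fix.

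**Conclusion.** The point holds in a limited form. The cotinine schedule contradicts itself, with two sections on each side. CO has a cutoff and a visit schedule but no part in the primary endpoint. Case A counts as abstinent under both schedules and both readings of the definition, and under the literal 'and' denial is enough even with positive cotinine at month 12.

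These conclusions follow from the text and need no assumed numbers. The cotinine window of about 1 to 4 days rests on assumed levels and cutoffs. The size and direction of any bias in the treatment comparison cannot be derived from the documents. It is worth correcting because it concerns the primary endpoint and the data needed are already planned.

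**What to change.** 1. Reconcile sections D and I with section J and the budget, so that there is one cotinine schedule. The four tests are already budgeted.
2. Reword section E so that each of the following alone makes a participant non-abstinent. Self-report counts from the quit date. The biochemical tests count once the participant is past both the quit date and the end of study nicotine.
   - self-reported smoking;
   - CO above 6 ppm at month 6, 9 or 12, even if smoking is denied;
   - positive cotinine at month 12, even if smoking is denied.
3. Let a positive month 6 cotinine count in the same way only for participants no longer using nicotine products, and record that use at the visit.
4. Report the endpoint without the CO rule as a sensitivity analysis.

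No new measurement is needed beyond a record of nicotine use, since CO and the four kits are already planned. The change does tighten the primary endpoint. Expect a slightly lower abstinence rate and some false positives from other sources of CO. Relapse between visits will still go undetected, and the report should say so.

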**F. Secondary outcomes:**

Secondary outcomes of interest at the final follow-up will include number of quit attempts since enrollment, the number of smoked cigarettes/bidis per day (for those who were not able to quit), duration of use of intervention. The tobacco use outcomes will be smoking excess, smoking reduction, continued use and relapse from the baseline information. Interim smoking cessation outcomes at 3 and 6 months of intervention will be assessed.

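### Salivary cotinine verifies smoking status at month 3, when the experimental arm is still on scheduled nicotine replacement, so the month-3 interim outcome can misclassify treated quitters

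*Protocol*

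**What the plan says.** Section D (Intervention and Control arm) makes cotinine the deciding test: "Saliva cotinine test results will be considered as the biochemical verification for smoking status". Exhaled carbon monoxide (CO) has a supporting role: "carbon monoxide levels will be a complementary test to support the evidence for smoking status of the participants". The reason given is that CO is less sensitive. The same paragraph describes salivary cotinine as an "indicator of tobacco use, exposure to secondhand smoke or use of pharmaceutical nicotine", with a half-life of 15 to 19 hours.

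The documents disagree on when cotinine is taken:
- Section D: "saliva cotinine test will be done to assess the smoking status of the participants during baseline and end-line of the study". Section I (Study tools) likewise gives only the start and end of follow-up.
- Section J (Therapy protocol), cotinine row, both arms: "0-day, Month- 3, 6, 12". The budget justification provides four kits per participant at those same times.

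On outcomes, section F says: "Interim smoking cessation outcomes at 3 and 6 months of intervention will be assessed". Section E places the primary outcome 12 months after the intervention starts. It defines non-abstinence as self-reported smoking at any time in the intervention or follow-up *and* a positive cotinine test.

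On treatment, the section J table gives the experimental arm patch for 4 weeks before and 12 weeks after the quit date, and the control arm patch for 12 weeks after it. Both arms have gum for the 12 weeks after the quit date. The budget repeats 16 and 12 weeks of patch. The Background explains that preloading means using the drug before quitting while still smoking as usual.

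**The concern.** By the protocol's own account, the verifying test cannot tell a smoker from someone using nicotine patch or gum. That does no harm once treatment has ended, but the month-3 test falls inside the experimental arm's scheduled course. An adherent experimental quitter can then be recorded as a smoker because the study drug is present. If the control arm has already finished, the error falls on one arm only and works against the intervention under test.

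At stake is the month-3 interim outcome and any analysis that uses it. The timeline schedules interim data analysis and publications for July to December 2023, before follow-up ends in June 2024. If more than 10% of data are missing, the Results section calls for a mixed-effects logistic model for repeated binary data, which would plausibly include the month-3 values.

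**Working it through.** **Plan's own figure.** The sample size is not touched by this point, but its rates are used below. With 47.5% vs 27.5%, two-sided 5%, 80% power, pooled variance and no continuity correction:
n = [1.960·√(2·0.375·0.625) + 0.842·√(0.475·0.525 + 0.275·0.725)]² / 0.20² = 90.8, so 91 per arm, as stated.

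**Inputs for the timeline.** Patch course: (4 + 12)·7 = 112 days experimental, 12·7 = 84 days control (section J, budget). Month 3: days 90 to 92. Cotinine half-life: 15 to 19 h (section D).

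**Step 1. Clock from the start of intervention (sections E and F), control quit date at day 0.**
- Experimental: 112 − 92 = 20 to 112 − 90 = 22 days of treatment remain. Days since quitting: 90 − 28 = 62 to 92 − 28 = 64, about week 9 of 12 after the quit date. Patch and gum are both still scheduled.
- Control: treatment ended 90 − 84 = 6 to 92 − 84 = 8 days earlier. In half-lives: 6·24/19 = 7.6 to 8·24/15 = 12.8. The remaining fraction of treatment cotinine is 0.5^7.6 ≈ 0.5% down to 0.5^12.8 ≈ 0.01%, which is negligible.

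So treatment-related positives arise in the experimental arm and essentially not in control.

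**Step 2. Other readings of the clock.**
- Control quits q days after day 0: its course ends at day q + 84, so it is still on treatment at month 3 once q exceeds 6 to 8 days. The test is then uninformative in both arms.
- Months counted from the quit date: the experimental test falls on days 28 + 90 = 118 to 28 + 92 = 120, which is 6 to 8 days after day 112. Both arms have finished and the problem largely disappears.

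**Step 3. Does the section E definition block the error?**
- Read as *and*: experimental participants smoke during preloading, which is smoking during the intervention. A cotinine result that is positive from treatment then completes the definition of non-abstinence.
- Read as *or*: the positive cotinine alone is enough.

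**Step 4. Size (illustration only).** Assume that the section G rates, which are 6-month rates, applied at month 3; that actual smokers are classified correctly; that control is off treatment; and that a share f of experimental abstainers is counted as smoking only because of treatment. The documents do not give f.
Apparent difference = 0.475·(1 − f) − 0.275.

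| f | Experimental rate | Difference (points) |
|---|---|---|
| 0 | 47.5% | +20.0 |
| 25% | 35.6% | +8.1 |
| 42% | 27.5% | 0 (f = 1 − 0.275/0.475 = 0.421) |
| 50% | 23.8% | −3.8 |
| 100% | 0% | −27.5 |

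If both arms are on treatment with the same f, the difference is 20·(1 − f): 15, 10 and 0 points at f = 25%, 50% and 100%. It shrinks but does not reverse.

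**Step 5. Later visits.** Month 6 is about day 26·7 = 182, which is 182 − 112 = 70 days after the experimental course and 182 − 84 = 98 days after the control course if control quit at day 0. Month 12 is later still.

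**The case against.** The strongest counter-argument is that section D, read alone, takes cotinine only at baseline and the end, so the verification sentence may concern only those points. Section J lists a month-3 test without saying that it decides the interim outcome, and section F does not define interim cessation; a SAP not shown may do so. This softens the point but does not remove it. The table and the budget both schedule the month-3 test, section D names no other verifier, and nothing in the protocol exempts visits during treatment.

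The contrast between arms is conditional, and that objection stands. No section ties the quit date to day 0, and section D lets counselling continue until a participant is ready to quit. Section D also describes regimens of 12 weeks in both arms, with gum alone in control. This contradicts section J, the budget and section 6, and must be reconciled. The working follows section J without judging which regimen is intended.

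A reader might infer three stronger things that the documents do not support:
- *The primary outcome is biased too.* Scheduled treatment ends well before months 6 and 12. Recording duration of use as a secondary outcome does not show use beyond schedule, and the budgeted patches barely exceed the course (120 for 112 days, 90 for 84). Nor would the month-12 error equal the share of abstainers still using nicotine replacement: that needs cotinine alone to decide, whereas section E says *and*.
- *The artefact is about 40 points.* Assuming 50% abstinent in both arms and 80% of experimental abstainers still on treatment gives 0.50·(1 − 0.80) = 10% vs 50%. Neither share is in the documents, and the sum ignores the *and*.
- *CO is simply the better test and was wrongly demoted.* Section D gives a reason, lower sensitivity, which has force at visits after treatment has ended.

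**Conclusion.** The point holds for month 3. The plan verifies smoking status with a test that it says responds to the study drug, and schedules it at about day 91 of a 112-day experimental course. On the stated clock, with control participants quitting at day 0, the misclassification runs against the experimental arm. If control participants quit more than about a week later, the test is uninformative in both arms. If months run from the quit date, little remains.

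The size depends on the unknown share of experimental abstainers who test positive from treatment. On the illustrative rates, about 42% would erase a 20-point benefit, and larger shares would reverse its sign. Under the *and* definition this also requires smoking during preloading to count as smoking during the intervention.

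Severity is moderate. It is limited to the month-3 interim outcome and any interim or longitudinal analysis that uses it. The 12-month primary outcome and the sample size are unaffected by scheduled treatment.

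**What to change.** - Verify the month-3 interim outcome by the exhaled CO already scheduled at that visit, with the protocol's cut-off of six ppm or less. Patch and gum deliver nicotine without smoke, so they do not produce the false positive at issue.
- Keep cotinine as the verifier at months 6 and 12, after scheduled treatment has ended. Do not switch tests there according to self-reported nicotine replacement use: a smoker who claimed such use would get the less sensitive test.
- State one time origin for the 3-, 6- and 12-month assessments relative to the quit date. Say there whether smoking during preloading counts, because changing the verifier does not settle that wording.
- Reconcile sections D and I (cotinine at start and end only) with section J and the budget (months 0, 3, 6 and 12).

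The cost is wording only. CO is already measured at month 3, and no treatment changes. The drawback is the one section D names: CO is less sensitive than cotinine, so some smokers will be missed at month 3. If the month-3 cotinine test is dropped, one kit per participant (8 dollars) is saved.

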**E. Primary Outcomes:**

The primary clinical outcome will be the binary smoking cessation; abstinence or non-abstinence assessed at 12 months from the starting point of intervention. Non-abstinence will be defined as self-reported smoking anytime during the intervention or follow up and a positive salivary cotinine test.

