When a person stops using tobacco, the aim of NRT is to replace the nicotine that the smoker would have been receiving, without the additional harmful elements of tobacco.[7]. With fast acting drugs such as nicotine gum, the nicotine is absorbed through buccal mucosa and reaches peak plasma nicotine concentrations within 15–30 min (as compared to within 1–2 min after smoking) and the blood levels reach a flat peak after about 30 minutes of chewing [8]. On the contrary, trans-dermal patches release nicotine more gradually with peak concentrations within hours after application [9]. As a result, none of the available NRT products deliver such high doses of nicotine as quickly as cigarettes. One implication is that combination NRT (fast-acting form + patch) results in approximately 15% to 36% higher long-term quit rates than a single form of NRT. [7]

Using a nicotine replacement treatment (or other smoking cessation drugs) before a quit attempt while smoking normally is called preloading. A systematic review showed limited evidence that nicotine preloading may be effective, but with unexplained heterogeneity between studies. Some studies suggested that nicotine preloading doubled the likelihood of achieving abstinence, while other studies suggested that preloading had no effect [10]. However, more evidence is needed to determine the effectiveness of preloading combination NRT when compared with standard regimen [7]. This study intends to determine and gather further evidence about the effectiveness of preloading combination NRT among adult smokers of Kazakhstan.

**Research question:** What is the effectiveness of preloaded combination nicotine replacement therapy on smoking cessation?

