| Nicotine Replacement Therapy for > 20 cigarettes per day                 | 
Nicotine Patch: Preloading for 4 weeks + 12 weeks post quit date
 
 
- 21 mg: 4 weeks before and after quit date
 
- 14 mg: Next 4 weeks
 
- 7 mg: Last 4 weeks
 
 
Nicotine chewing gums 4 mg for 12 weeks post quit date
(12/day on week 1.....1/day on week 12)
 | 
Nicotine Patch: 12 weeks post quit date
 
 
- 21 mg: 4 weeks after quit date
 
- 14 mg: Next 4 weeks
 
- 7 mg: Last 4 weeks
 
 
Nicotine chewing gums 4 mg for 12 weeks post quit date
(12/day on week 1.....1/day on week 12)
 |
| Nicotine Replacement Therapy for < 20 cigarettes per day                 | 
Nicotine Patch: Preloading for 4 weeks + 12 weeks post quit date
 
 
- 21 mg: 4 weeks before and after quit date
 
- 14 mg: Next 4 weeks
 
- 7 mg: Last 4 weeks
 
 
Nicotine chewing gums 2 mg for 12 weeks post quit date
(12/day on week 1.....1/day on week 12)
 | 
Nicotine Patch: 12 weeks post quit date
 
 
- 21 mg: 4 weeks after quit date
 
- 14 mg: Next 4 weeks
 
- 7 mg: Last 4 weeks
 
 
Nicotine chewing gums 2 mg for 12 weeks post quit date
(12/day on week 1.....1/day on week 12)
 |
| CO monitoring, Fagerstorm score, smoking frequency, medication adherence | 0-day, Month- 1, 3, 6, 9, 12                                                                                                                                                                                                                                                                                                                 | 0-day, Month- 1, 3, 6, 9, 12                                                                                                                                                                                                                                                                             |

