**Conclusion:**

This study focuses on determining the effectiveness of preloaded combination nicotine replacement therapy on smoking cessation of adult population. The study results shall add scientific evidence to the available literature about the preloaded combination nicotine replacement therapy being an effective. The study protocol through publication in leading journals assists future researchers in this area of interest to adopt certain or most of the aspects of the study protocol relevant to their methodology and research setup.

**Flow diagram: Preloading combination Nicotine Replacement Therapy trial**[figure not shown]

The Principal Investigator (PI) shall be the technical, administrative, and financial decision maker for the research project. The co-PI shall work in partnership with the PI and the other team members such as master's degree holders and students shall assist both the PI and the co-PI. The PI shall be the competent authority to report to the organizations about the progress, modifications, adverse reactions, or any other issues that arise during the course of the project.

The Infrastructure for the study will be setup in 60 days from January 2022 to April 2022. A room size of 500/600 square feet will be identified at the cardiac research center for counselling & treatment for the participants.

The trial begins from April 2022 and is proposed to end in June 2024 including the follow up of the last recruited participant. The duration of the trial including follow up is 12 months.

| TITLE                                       | START      | FINISH     | DURATION | 2022 |   |   |   |   |   |   |   |   |    |    |    | 2023 |   |   |   |   |   |   |   |   |    |    |    | 2024 |   |   |   |   |   |   |   |   |    |    |    |
|---------------------------------------------|------------|------------|----------|------|---|---|---|---|---|---|---|---|----|----|----|------|---|---|---|---|---|---|---|---|----|----|----|------|---|---|---|---|---|---|---|---|----|----|----|
|                                             |            |            |          | 1    | 2 | 3 | 4 | 5 | 6 | 7 | 8 | 9 | 10 | 11 | 12 | 1    | 2 | 3 | 4 | 5 | 6 | 7 | 8 | 9 | 10 | 11 | 12 | 1    | 2 | 3 | 4 | 5 | 6 | 7 | 8 | 9 | 10 | 11 | 12 |

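### Smoking is counted from the start of the intervention, which in the experimental arm includes four weeks of planned smoking, so the primary outcome does not judge the two arms by one rule

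*Protocol*

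**What the plan says.** Section E (Primary Outcomes) fixes the time origin as "abstinence or non-abstinence assessed at 12 months from the starting point of intervention". It then gives the failure rule: "Non-abstinence will be defined as self-reported smoking anytime during the intervention or follow up and a positive salivary cotinine test". Section F applies the same clock to the interim cessation outcomes at 3 and 6 months and gives no separate definition for them.

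The Background explains the experimental strategy: "Using a nicotine replacement treatment (or other smoking cessation drugs) before a quit attempt while smoking normally is called preloading". In the section J therapy table the experimental column reads "Nicotine Patch: Preloading for 4 weeks + 12 weeks post quit date" and the control column reads "Nicotine Patch: 12 weeks post quit date". The budget justification costs patches for 16 weeks in one arm and 12 in the other. Section 6 (Research environment) places preloading in the experimental group.

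Nowhere does the protocol exclude smoking before the quit date, allow a grace period, tie outcome visits to the quit date, or say when the control arm's quit date falls relative to day 0. Section D describes the arms differently: both at 12 weeks, no preloading, and gum alone for controls.

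**The concern.** A participant who follows the experimental regimen in section J has smoked during the intervention, because preloading requires it. Half of a two-part failure rule is then satisfied for everyone in that arm before the quit attempt begins, and it can no longer separate quitters from relapsers there. In the control arm, where nicotine replacement begins at the quit date, the same half still works.

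The result is misclassification that depends on the allocated arm, in the primary outcome. The section K comparisons cannot detect or remove it. With no treatment effect at all it would produce a difference between arms. With a real effect it would shrink the difference.

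The clock raises a second, smaller issue. A visit at a fixed time from the start of treatment falls four weeks earlier after quitting in any arm that preloads for four weeks.

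**Working it through.** **The plan's own figure.** Section G uses 47.5% versus 27.5%, two-sided 5%, 80% power. With pooled variance and mean rate 0.375: n = [1.96·√(2·0.375·0.625) + 0.8416·√(0.475·0.525 + 0.275·0.725)]² / 0.20² = 90.8, so 91 per arm, as stated. Nothing below changes that figure. The question is whether the outcome, as defined, can show the 20 points.

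**Who is classified as a failure.** Take the section G rates as true abstinence and assume no loss. Two inputs are not in the documents and are assumed: 10% of smokers are cotinine-negative at month 12, and a share *d* of relapsers deny smoking at every visit, independently of cotinine. True abstainers are assumed to be classified correctly. The chance that a smoker is wrongly read as abstinent is then:

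- experimental arm, rule as written (cotinine only): 0.10
- control arm, rule as written (admits and positive): 1 − 0.9(1 − *d*), which is 0.145, 0.190 or 0.280 for *d* = 5%, 10%, 20%

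**No true effect (27.5% in both arms).** The experimental arm reads 0.275 + 0.725·0.10 = 34.8%. The control arm reads 38.0%, 41.3% or 47.8%. The false deficit is 0.725·0.9·*d* = 3.3, 6.5 or 13.1 points. It is due entirely to the asymmetry, since equal rules would give zero.

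**True effect of 20 points.** The experimental arm reads 0.475 + 0.525·0.10 = 52.75% under the rule as written. If the self-report criterion worked in both arms, the observed difference would be 20·0.9(1 − *d*). The gap between the two is 0.525·0.9·*d*.

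| *d* | Difference as written | Difference, same 'and' rule in both arms | Lost to asymmetry | Lost to 'and' rule and missed cotinine, both arms |
|---|---|---|---|---|
| 5% | 14.7 | 17.1 | 2.4 | 2.9 |
| 10% | 11.5 | 16.2 | 4.7 | 3.8 |
| 20% | 4.95 | 14.4 | 9.45 | 5.6 |

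If either criterion counted as failure and smoking were counted only from the quit date, a smoker would be missed only when denying and cotinine-negative (0.10·*d*). The difference would be 20·(1 − 0.10·*d*) = 19.9, 19.8 or 19.6 points.

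**'Or' without a quit-date anchor.** Every experimental participant who truthfully reports smoking during preloading is a failure, so abstinence in that arm is about 0%.

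**The clock, if control participants quit on day 0.** Twelve months is 365.25/7 = 52.2 weeks, so the experimental arm is seen 48.2 weeks after quitting and the control arm 52.2. Month 6 is about 22 versus 26 weeks, and month 3 about 9 versus 13. The documents give no relapse rate. Assume 10% to 40% of 6-month abstainers relapse by month 12 at a constant rate *r*, with S(w) = S₆·(1 − *r*)^((w − 26.1)/26.1). Then S(48.2) − S(52.2) is 0.4 to 1.3 points from a 27.5% base and 0.7 to 2.3 points from 47.5%. This favours the experimental arm, against the direction of the failure rule.

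**Month 3.** At about 9 weeks after quitting, an experimental participant is still inside the 12 weeks of patch and gum, while a control participant at 13 weeks has finished. Section D itself notes that cotinine also reflects pharmaceutical nicotine. If section E's definition is carried to month 3, a truly abstinent experimental participant can meet both criteria.

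**The case against.** **The control quit date is not stated.** A reader might take 48 versus 52 weeks, and smoke-free controls, as given facts. They are not. The control column of section J counts 12 weeks from a quit date that is not placed relative to day 0. Brief advice starts on day 0 in both arms, and section D offers repeated weekly counselling to anyone not yet willing to quit. Section D also describes both arms without preloading. This stands, so the clock figures are one scenario, although the natural reading of section J. It does not rescue the failure rule: if both arms quit after day 0, smoking before the quit date voids the self-report criterion for everyone, and the same repair is needed.

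**The 20-to-5 inference.** A reader might infer from the last table row that the asymmetry turns a 20-point effect into 5 points. It does not. Of the 15.05 points lost, 5.6 come from requiring both criteria and from missed cotinine, which affect both arms. The asymmetry accounts for 9.45.

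**The denial rates are assumed.** Neither input is in the documents, and 20% is the upper end. Smoking frequency is recorded on day 0 and at months 1, 3, 6, 9 and 12, so an early relapser would have to deny smoking repeatedly. This argues for the lower rows, but does not bring the loss to zero.

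**The biases oppose each other.** True, but nothing makes them cancel, and the clock effect is small at month 12.

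**Conclusion.** The point holds. On the regimen in section J, the self-report criterion is met by design in the experimental arm, which is then judged on cotinine alone, while a control participant whose treatment starts at the quit date must also admit smoking. With 10% of smokers cotinine-negative and 5% to 20% of control relapsers denying, the asymmetry alone costs about 2.4 to 9.45 points of a true 20, or creates a deficit of 3.3 to 13.1 points where there is no effect. The direction follows from the text; the size rests on those assumed rates.

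A reader might also infer that preloading makes every experimental participant a failure under the current text. It does not, because a positive cotinine test is required as well; that outcome arises only if 'and' is read as 'or'. The clock difference is conditional on a day-0 control quit date and on its own would be a minor point.

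This should be settled before outcome data are classified, because the protocol itself fixes the definition and later analysis cannot reliably undo arm-dependent misclassification.

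**What to change.** In both arms:

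- define the target quit date relative to randomisation;
- count smoking only from that date, stating that smoking during preloading does not count;
- classify participants who never make a quit attempt as non-abstinent, so that nobody drops out of the intention-to-treat comparison;
- time the 3-, 6- and 12-month outcomes from that date. Month 3 then falls at about 13 weeks after quitting, beyond the 12 weeks of treatment, in both arms.

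Correct the 'and' in section E in the same amendment, so that either reported smoking or a positive cotinine test means non-abstinence. Anchoring alone would leave 14.4 of 20 points in the 20%-denial scenario. Do not change the 'and' without the anchor.

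Sections E, F and J (including the visit, quality-of-life and cotinine schedules) and the project timetable need matching edits. Section D's description of the arms must be reconciled with section J, the budget justification and section 6; which description is right is for the sponsor to settle.

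The change is mostly wording, with one real cost. If the last participant is recruited on 2023-06-24 and preloads for four weeks, the last 12-month visit is 2023-06-24 + 28 + 365 days = 2024-07-21. The protocol says the trial "is proposed to end in June 2024 including the follow up of the last recruited participant", so that end date must move. The visit would fall 27 days into the final-analysis window of 2024-06-24 to 2024-08-22, leaving about one month with complete data.
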